**13. Safety assessment**

Although auricular acupuncture is typically regarded as a safe treatment, participants will be assessed for any discomfort. Details of all adverse events will be recorded during the trial in the case report forms (CRFs). The ethics committee will examine any connections between adverse events and the intervention and make a decision on whether the study should be continued.

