**4. Trial process chart**

| Outcomes | Evaluation time | | |
| --- | --- | --- | --- |
|  | Baseline | 4 weeks after allocation | 8 weeks after allocation |
| Blood pressure | × | × | × |
| phlegm-dampness constitution score | × | × | × |
| Proteins of the RAS | × |  | × |
| Gene polymorphism testing (only intervention group) | × |  |  |

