**12. Outcomes**

**Main outcome**

**Efficacy of auricular acupuncture:** The blood pressure will be measured at baseline, 4 weeks and 8 weeks after allocation. The efficacy of auricular acupuncture is defined as office diastolic blood pressure is reduced to a threshold set out in “Guiding Principles for Clinical Research of New Chinese Medicines” formulated by the Ministry of Health of the Peoples Republic of China a significant effect means a diastolic blood pressure decrease ≥10 mmHg and return to normal level or a decrease ≥ 20 mmHg. An effect means a diastolic blood pressure decrease <10 mmHg and return to normal level or decrease of 10 to 20 mmHg. Invalid means that the change in blood pressure did not reach the “effect” level described above.

Requirements for blood pressure measurement:

(1) blood pressure will be measured in the afternoon and in a quiet room with comfortable temperature (22℃-24℃) by one well-trained researcher.

(2) use validated upper-arm cuff device and sphygmomanometer for blood pressure measurement, and ensure the calibration before the measurement.

(3) Before measurements: remain seated and relaxed for at least 5 min; avoid smoking, caffeine and exercise for 30 min; empty bladder.

(4) Sit in a backrest chair with back supported on chair, legs uncrossed and feet flat on floor, arm resting on table with mid-arm at heart level.

(5) Tie the cuff to the upper arm, and tighten it so that it can be inserted 1 to 2 fingers. The lower edge of the cuff should be 2.5cm above the elbow fossa.

(6) Blood pressure of both upper arms is measured at first visit and the higher side is usually measured later. At each visit take 2 measurements with 1-2 min between them. Calculate the average of the 2 measurements. If the 2 readings of systolic or diastolic blood pressure varied by more than 10mmHg, the third time is taken and the average of the last two measurements is recorded.

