**17. Operational approach**

Participants will be seated and the skin on the auricular acupoints will be sterilized with a 75% alcohol swab. A sterilized XS100-A acupoint detector will be used to probe and mark each acupoint. An adhesive patch (0.5 cm*0.5 cm) with Wangbuliuxing seeds will be taped on the points. Well-trained and certified auricular therapists will instruct all participants to apply pressure to each auricular acupoint using their thumb and index finger until they feel pain and heat. Participants will be supported to self-perform acupressure 20 to 30 times on each auricular acupoint, three times daily. Auricular acupuncture will be carried out on the auricular acupoints on one ear in one visit and the opposite ear in the following visit. The adhesive patch will be replaced by the researcher every three days over the eight-week duration of the trial.

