**19. Participants’ management**

- Record the participants’ name, contact information and other information, and keep the information confidential.
- Add the participants’ WeChat, put intervention group into the group chat, and remind them to press the ear point every day.
- Before the trial, the investigator fully informed the participants, respected their wishes and signed the informed consent.

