**23. Treatment and management of the participants after the trial**

Participants in the control group who did not receive auricular acupuncture will be treated by a free 2-month auricular acupuncture service.

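### Adverse events have no common collection schedule while researcher contact differs sharply by arm, so any between-arm comparison of non-local events is open to ascertainment bias

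*Protocol*

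**What the plan says.** Protocol section 13 (Safety assessment) is the whole of the safety plan. It says that "participants will be assessed for any discomfort" and that "Details of all adverse events will be recorded during the trial in the case report forms (CRFs". On use of the records it says: "The ethics committee will examine any connections between adverse events and the intervention and make a decision on whether the study should be continued". It gives no visit, no standard question and no look-back period.

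Contact with participants is set elsewhere:

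- **Both arms.** Section 12 (Main outcome): "The blood pressure will be measured at baseline, 4 weeks and 8 weeks after allocation". The process chart in section 4 has the same three time points and no row for adverse events.
- **Intervention arm only.** Section 17: "The adhesive patch will be replaced by the researcher every three days over the eight-week duration of the trial". Section 19 tells staff to "put intervention group into the group chat, and remind them to press the ear point every day".
- **Control arm.** Section 23: "Participants in the control group who did not receive auricular acupuncture will be treated by a free 2-month auricular acupuncture service". Controls therefore have no patches to replace during the trial, even though section 17 speaks of instructing all participants. Section 19 has the WeChat contact of participants added without limiting this to one arm.

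Section 18 names a between-group test for efficacy and none for adverse events.

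**The concern.** If the protocol is followed to the letter, the number of occasions on which a participant can mention an event depends on the arm. Someone in the intervention arm meets a researcher about every third day. A control has two defined visits after baseline. A passing headache, a dizzy spell or a bad night's sleep has many more chances of being recorded in one arm than in the other, even if auricular acupuncture causes none of them.

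For reactions at the patch site this hardly matters, because controls have no patch and close observation of treated ears is useful. For non-local events the control arm is the natural background, and the contact structure would under-count it. If a report later sets adverse event counts side by side, or if the ethics committee looks to control events as background, treated participants could appear to have an excess that comes from contact frequency alone. This has to be settled in trial conduct: no later analysis can recover control events that nobody asked about.

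**Working it through.** The protocol gives no adverse event rate, event duration or count of contacts, so there is no figure of its own to reproduce. The calculation uses the contact schedule and, for one illustration, the 40 participants per group from section 9.

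**Step 1. Contacts over 8 weeks (56 days).**

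- Patch visits: 56 / 3 = 18.7. Counting from day 0, visits fall on days 0, 3, ..., 54, which is 19 in all and 18 after day 0.
- Adding the assessments on days 28 and 56, neither a patch day on this count: 18 + 2 = 20 contact days after baseline in the intervention arm.
- Controls: 2 defined visits after baseline.
- Ratio: 20 / 2 = 10. With baseline counted in both arms it is 21 / 3 = 7. Chat messages are not counted.

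**Step 2. Chance that an event is recorded if there is no recall.** Assume equal true event rates, and that an event lasting d days is recorded only if it is present at a contact. With contacts k days apart, the chance is min(1, d/k), where k = 3 for the intervention arm and k = 28 for controls.

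| Duration d | Intervention | Control | Ratio |
|---|---|---|---|
| 1 day | 1/3 = 0.333 | 1/28 = 0.036 | 9.3 |
| 3 days | 1 | 3/28 = 0.107 | 9.3 |
| 7 days | 1 | 7/28 = 0.25 | 4.0 |
| 14 days | 1 | 14/28 = 0.50 | 2.0 |

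Using the exact contact days (patch days plus days 28 and 56) moves the one-day figures to 36% against 4% and leaves the others essentially unchanged.

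**Step 3. In participants.** Assume a true event rate of 20% in both arms, so 0.20 × 40 = 8 events each. With the exact contact days, the recorded events would be 2.9 against 0.3 (1 day), 8.0 against 0.9 (3 days), 8.0 against 2.0 (7 days) and 8.0 against 4.0 (14 days).

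**Step 4. Effect of recall.** Let a fraction r of the events that were not present at a contact be recalled and recorded anyway, the same r in both arms. The chance becomes p + r(1 − p), with p from Step 2.

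| Duration | r = 0 | r = 0.5 | r = 1 |
|---|---|---|---|
| 1 day | 9.3 | 0.667/0.518 = 1.3 | 1 |
| 3 days | 9.3 | 1/0.554 = 1.8 | 1 |
| 7 days | 4.0 | 1/0.625 = 1.6 | 1 |
| 14 days | 2.0 | 1/0.75 = 1.3 | 1 |

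The durations, the 20% rate and r are assumptions; only the contact intervals and the group size come from the protocol. Equal r also simplifies matters: recall over three days may be better than recall over four weeks, which would widen the gap again.

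**The case against.** The strongest reply is that the comparison in question is not in the plan. Safety is neither a research purpose (section 6) nor an outcome (section 12), and section 18 tests only efficacy between groups. A reader might infer that a planned safety analysis is biased, or that the decision to continue the study rests on a comparison of arm rates. The protocol supports neither. Section 13 can be read just as naturally as a review of each event for its link to the intervention, and it mentions no arm-level summary. This stands, and it limits the point to comparisons or background use that may be made later.

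A reader might also infer that controls have no contact outside the three assessments. That goes too far. Control procedures are not described in the text at hand, the design figure in section 8 is not shown, and WeChat contact is added for participants in general, so controls can report on their own initiative. What remains is a difference between spontaneous reporting and frequent face-to-face contact.

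Three smaller objections are fair. The chart in section 4 lists outcome measurements, so the missing row does not show that adverse events go unasked at weeks 4 and 8. Section 13 calls for all events to be recorded, which would cover events already over when reported, so the no-recall assumption is an extreme. In section 19, the daily frequency may describe the pressing rather than the reminder. The three-day patch visits carry the point without the chat.

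It is not an answer that a statistical analysis plan may fill the gap. When and how events are elicited is trial conduct, and the imbalance comes from the protocol's own visit structure.

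**Conclusion.** The point holds in a limited form. The protocol sets no common time points or question for adverse events, and it gives the intervention arm about 20 contact days after baseline against 2 defined visits for controls. Any between-arm comparison of non-local events, or any use of control events as background when a connection with the intervention is considered, is open to ascertainment bias toward more recorded events in the intervention arm.

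The size cannot be fixed from the document. The 4- to 9-fold excess is the no-recall upper bound for events of 1 to 7 days, given recall that is equal in both arms. It shrinks with longer events and better recall, and disappears with full recall. It should not be read as an expected excess. The finding rests on taking the three assessments as the controls' only scheduled visits, which is inferred from the text.

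The efficacy outcome and the sample size are not touched. The matter should be corrected, but it does not threaten the main result.

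**What to change.** Add an adverse event row at weeks 4 and 8 to the process chart in section 4, and state the following in section 13:

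1. Both arms are asked the same adverse event question at the existing week 4 and week 8 visits, covering the whole interval since the last assessment.
2. Any between-arm summary of adverse events uses those answers only.
3. Events first reported at patch visits or by chat are still recorded and still passed to the ethics committee, but they are listed separately and not compared with controls.

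The question is best asked after blood pressure has been recorded, because an answer about the ear could reveal the arm to the assessor, whom section 11 keeps blinded.

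The cost is one chart row and one case report form question at visits that already take place. The downside is some recall loss in the compared data, since short, mild events may be forgotten over four weeks. That loss should be more alike in the two arms than under the present wording, though frequent contact may still help intervention participants to remember.

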**14. Recruitment**

Bulletin board advertisements will be posted, and community doctors will be contacted to recruit participants. The recruitment information will mainly include the study eligibility criteria and researcher contact details. A well-trained investigator will be responsible for the recruitment of participants. The recruitment will be conducted at Qingbo Street Community Health Service Center from September 2022 to February 2023. After the study procedures have been fully explained, the investigator will obtain and archive the informed consent forms from the participants that meet the eligibility criteria.

**15. General information of the participants**

Chronological age; height; waist/hip circumference; gender; occupation; weight; body mass index (BMI); blood pressure (SBP/DBP); past history; family history; medications (The current drug use of patients for hypertension and other diseases).

**16. Baseline indicators and observation items**

Demographics include age, gender, height, weight, body mass index, waist/hip circumference, smoking history, and drinking history.

**17. Operational approach**

Participants will be seated and the skin on the auricular acupoints will be sterilized with a 75% alcohol swab. A sterilized XS100-A acupoint detector will be used to probe and mark each acupoint. An adhesive patch (0.5 cm*0.5 cm) with Wangbuliuxing seeds will be taped on the points. Well-trained and certified auricular therapists will instruct all participants to apply pressure to each auricular acupoint using their thumb and index finger until they feel pain and heat. Participants will be supported to self-perform acupressure 20 to 30 times on each auricular acupoint, three times daily. Auricular acupuncture will be carried out on the auricular acupoints on one ear in one visit and the opposite ear in the following visit. The adhesive patch will be replaced by the researcher every three days over the eight-week duration of the trial.

**18. Statistical analysis**

The statistician will use SPSS 25.0 software to analyze the data; a *P*-value < 0.05 will be considered statistically significant. Continuous variables will be expressed as means and standard deviations, or as medians and interquartile ranges. Categorical variables will be expressed as frequencies. Continuous variables will be analyzed by *t* tests or Wilcoxon rank-sum tests. The difference before and after treatment in each group will be determined using a paired *t* test. A chi-squared or Fisher’s exact test will be used to compare the efficiency between the intervention and control groups.

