**6. Research purposes**

(1) The changes of proteins of the RAS before and after auricular acupuncture will be compared to explore the mechanism underlying the effect of auricular acupuncture on blood pressure.

(2) Participants in the intervention group will have gene polymorphism testing, the changes in blood pressure of different genotypes will be analyzed to determine whether genotype influence the blood pressure-decreasing response to antihypertensive treatment with auricular acupuncture. And to identify genes of RAS that are sensitive to auricular acupuncture.

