**8. Study design**

Randomized controlled trial, parallel

[figure not shown]

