**9. Sample size calculation**

The sample size for this RCT has been computed based on our previous study (36). In our previous study, the efficacy rate was 28% in the intervention group and 0% in the control group after eight weeks of auricular acupuncture intervention. Setting an α-value of 0.05 and a β-value of 0.10, the sample size was calculated using the following formula:

$$n=\frac{{2\bar{p}\bar{q}\left( z_{\alpha}+z_{\beta} \right)}^{2}}{\left( p_{1}-p_{2} \right)^{2}}$$

Considering a dropout rate of 20% during the research, a total of 40 participants per group will be enrolled in the study, for a total required sample size of 80.

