**Secondary outcomes**

(1) **PDC score:** Patients’ PDC score will be determined by TCM physicians using the TCM Constitution Scale compiled by [name] in 2009. This scale consists of nine subscales. The original score of the PDC subscale is equal to the sum of the scores for each item, and the transformed score is calculated as follows: [(original score - number of items)/(number of items × 4)] ×100. PDC score will be measured at baseline, 4 weeks and 8 weeks after allocation, and the transformed score will be recorded.

(2) **Proteins of the RAS** **ACE、AngⅡ、ACE2、Ang (1-7):** Serum concentrations of ACE, AngⅡ, ACE2, Ang (1-7) will be tested using enzyme-linked immunosorbent assay. The participants will be required to avoid drinking alcohol and intense exercising one day before sample collection. Females should avoid having their menstrual period during collection. Serum will be separated from the blood by centrifugation and will be stored at -80℃ until final analysis. Blood sample will be collected from each eligible participant at baseline and 8 weeks after allocation.

**(3) Office blood pressure of different genotypes:** Only participants in the intervention group will have gene polymorphism testing at baseline. Five single nucleotide polymorphisms (ACE, ACE2, AT1R, AT2R, Mas) will be genotyped by mass spectrometry or polymerase chain reaction. The changes in office blood pressure of different genotypes will be analyzed to determine whether genotype influence the blood pressure-decreasing response to antihypertensive treatment with auricular acupuncture.

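### Purpose 1 words the RAS mechanism question as a before/after change, and the only test tied to change is within-arm; the between-arm difference should be named as the analysis that answers it

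*Protocol*

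**What the plan says.** The design in section 8 is "Randomized controlled trial, parallel". Section 23 confirms that the control arm gets no auricular acupuncture until the trial is over.

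Purpose 1 in section 6 reads: "The changes of proteins of the RAS before and after auricular acupuncture will be compared to explore the mechanism underlying the effect". The control arm is not mentioned. Read literally, this contrast exists only in the intervention arm.

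The data cover both arms. Under secondary outcome (2) in section 12, "Blood sample will be collected from each eligible participant at baseline and 8 weeks after allocation", and four serum proteins are measured by ELISA: ACE, Ang II, ACE2 and Ang (1-7).

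Section 18 has three rules that bear on the point:
- Continuous variables are analysed by t tests or Wilcoxon rank-sum tests. The variables, time points or changes are not specified.
- Change has its own rule: "The difference before and after treatment in each group will be determined using a paired" t test.
- The chi-squared or Fisher test is the only one expressly described as comparing intervention with control, and it concerns the efficacy rate.

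For all of them, a P-"value < 0.05 will be considered statistically significant".

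**The concern.** The trial's title promises a RAS mechanism for the effect of auricular acupuncture on blood pressure, and purpose 1 is where that mechanism is to be shown. If purpose 1 is answered by the rule that section 18 attaches to change, the result is a P value for the intervention arm's own change over eight weeks. That change contains the effect of the intervention, if any, plus everything else that shifted in the same period.

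The protocol itself gives reasons to expect some shared change. Recruitment runs from September to February (section 14), so each week-8 sample falls later in the season than its baseline. Participants may be on medication for hypertension and other diseases (section 15), and section 7 excludes only ACE inhibitors and angiotensin receptor blockers among the antihypertensive drugs. The control arm is there to remove such influences, but it does so only if the two arms are compared.

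At stake is whether a mechanism could be declared from a movement in RAS proteins that untreated participants also show.

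**Working it through.** **Step 1: the plan's own figure.** Section 9 gives "Setting an α-value of 0.05 and a β-value of 0.10" and says that "the efficacy rate was 28% in the intervention group and 0% in the control group". With its formula, mean proportion 0.14 and two-sided alpha (sidedness is not stated):

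n = 2 × 0.14 × 0.86 × (1.960 + 1.282)² / 0.28² = 32.27 per arm

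Dividing by 0.8 for dropout gives 40.3, in line with "Considering a dropout rate of 20% during the research, a total of 40 participants per group will be enrolled in the study". The number rests on the binary blood pressure outcome, so it neither supports nor weakens the point about RAS proteins. Applying the 20% dropout to 40 leaves 40 × 0.8 = 32 completers per arm, which is used below.

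**Step 2: how often a within-arm test is significant with no treatment effect.** Assumptions: normally distributed changes, no treatment effect, and the same mean change d in both arms, in units of the SD of change. The protocol gives no SD or drift for any RAS protein, so d is shown as a range. The paired t statistic has 31 degrees of freedom, critical value 2.040 and noncentrality d × √32.

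| Drift d (SD of change) | Noncentrality | Intervention-arm paired test significant | Between-arm t test on change significant |
| --- | --- | --- | --- |
| 0 | 0 | 5% | about 5% |
| 0.1 | 0.566 | 8.5% | about 5% |
| 0.25 | 1.414 | 28% | about 5% |
| 0.5 | 2.828 | 78% | about 5% |

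The last column was checked by simulation and stays at 5% because equal drift cancels in the difference between arms. With all 40 per arm retained, the paired-test figures rise to 9.5%, 34% and 87% for d = 0.1, 0.25 and 0.5.

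**Step 3: what baseline adjustment adds.** Let r be the correlation between baseline and week 8 (not given, assumed 0.5 to 0.7), with equal variances at the two times. Relative variances of the arm difference are:

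- ANCOVA against week-8 values alone: 1 − r². This is 0.75 at r = 0.5 and 0.51 at r = 0.7, a reduction of 25% to 49%.
- ANCOVA against change scores: (1 − r²) / [2(1 − r)] = (1 + r)/2. This is 0.75 at r = 0.5 and 0.85 at r = 0.7, a reduction of 25% down to 15%.

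**Step 4: what the text does and does not fix.** The rank-sum test is an independent-samples test, and the paired test has a separate sentence. The general rule for continuous variables therefore reads as a two-sample comparison and would cover the RAS proteins. It does not say whether week-8 values or changes are compared, and nothing links it to purpose 1.

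**The case against.** The strongest reply is that the between-arm comparison is already in the plan. Section 18 lists two-sample tests for continuous variables, the proteins are sampled in both arms at both times, and an unadjusted two-sample comparison is valid in a randomised trial. The RAS proteins are a secondary outcome and purpose 1 is exploratory. Detail on covariates may sit in a statistical analysis plan that is not at hand. This stands to a large extent, and it limits both the claim and its severity.

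It also rules out several stronger readings that a reader might infer:
- **That the randomised comparison is discarded.** It is not; the two-sample tests are listed. What is missing is the statement that they answer purpose 1.
- **That the between-arm test ignores baseline.** The text does not say so. A two-sample test on changes uses baseline and is compatible with the wording.
- **That a mechanism will be declared when the intervention arm is significant and the control arm is not.** The protocol contains no such rule.
- **That skewed ELISA concentrations have no valid within-group test.** A paired t test depends on the distribution of the differences, not of the concentrations, so skewed concentrations do not by themselves invalidate it.
- **That regression to the mean or assay batches must be at work.** Eligibility does not select on RAS levels, and serum is frozen until final analysis, which is compatible with one assay run at the end. Season and co-medication are the better examples.

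The reply does not remove the wording of purpose 1. It is in the protocol itself, it describes a before/after contrast without a control, and the only rule expressly about change matches that wording. A separate plan specifying a between-arm analysis would leave the protocol's stated aim at odds with it.

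**Conclusion.** The point holds in limited form. Purpose 1 and the paired-test rule together allow a within-arm P value to be presented as the mechanism result, and such a P value does not measure an effect of auricular acupuncture. The protocol has the data and a two-sample test that could answer the question, but does not assign them to it.

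The error rates in the table depend on assumed drift. They are small if drift is small (8.5% at 0.1 SD) and large if it is moderate (78% at 0.5 SD). The documents do not show which applies. The conclusion that a between-arm test holds its level under equal drift does not depend on the size of the drift.

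This should be fixed but is not critical: the RAS proteins are a secondary outcome, and the primary efficacy rate is already compared between arms.

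**What to change.** - Reword purpose 1 in section 6 so that the question is the difference between the intervention and control arms in RAS proteins at week 8, given baseline.
- In section 18, name ANCOVA of each week-8 value, with its own baseline as covariate, as the inferential analysis for ACE, Ang II, ACE2, Ang (1-7) and the PDC score. Report the arm difference with a 95% confidence interval.
- State that within-arm changes are descriptive and are not used to judge an effect of auricular acupuncture.

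The cost is a few sentences. Every value needed is already collected in both arms at baseline and week 8, and the sample size stays at 40 per group.

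### The protocol names no between-arm outcome on mean DBP or SBP and states only unadjusted tests; baseline-adjusted week-8 DBP and SBP should be added as secondary outcomes

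*Protocol*

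**What the plan says.** - **Main outcome (section 12).** "The efficacy of auricular acupuncture is defined as office diastolic blood pressure is reduced to a threshold" taken from a national guideline. Each participant is graded as significant effect, effect or invalid, from the size of the diastolic fall and whether DBP returns to normal. SBP plays no part in the grading.
- **Secondary outcomes (section 12).** These are the constitution score, four serum proteins, and the change in office blood pressure by genotype. The genotype outcome exists in the intervention arm only, so it does not compare the arms.
- **Measurement (sections 4, 12 and 15).** "Blood pressure" is the first row of the process chart, under the column headed Outcomes, and is marked at baseline, week 4 and week 8. Section 15 records "blood pressure (SBP/DBP") among the general participant data.
- **Analysis (section 18).** For the response rate, a chi-squared or Fisher's "exact test will be used to compare the efficiency between the intervention and control groups". For the rest, "Continuous variables will be analyzed by *t* tests or Wilcoxon rank-sum tests", without saying which variables, which visit, or whether the value or the change is tested. A paired t test is planned within each group. No analysis uses the baseline value as a covariate.
- **Sample size (section 9).** In the group's previous study "the efficacy rate was 28% in the intervention group and 0% in the control group after eight weeks". "Setting an α-value of 0.05 and a β-value of 0.10" and "Considering a dropout rate of 20% during the research, a total of 40 participants per group will be enrolled" complete the inputs.

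**The concern.** The trial's title is about an effect on blood pressure, yet the only between-arm blood pressure outcome that section 12 defines is a diastolic category. Three things follow.

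First, grouping a continuous measure loses information. A fall of under 10 mmHg that crosses the normal limit is an effect, while a fall of 9 mmHg that stops above the limit is invalid.

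Second, the grade depends on baseline DBP, but the test ignores baseline. The inclusion criteria state no diastolic threshold. On a plain reading, a participant whose DBP is already normal cannot return to normal and can respond only through a fall of at least 10 mmHg.

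Third, no systolic comparison is fixed in advance. A systolic result would have to rest on a general sentence about continuous variables.

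At stake are the precision of the blood pressure result and whether mean DBP and SBP differences can be reported as plainly pre-specified.

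**Working it through.** **Step 1. Reproduce the planned size.** Inputs from section 9: p1 = 0.28, p2 = 0, so mean p = 0.14 and q = 0.86; α = 0.05, taken as two-sided (z = 1.960); β = 0.10 (z = 1.282).

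n = 2 × 0.14 × 0.86 × (1.960 + 1.282)² / 0.28² = 32.3, so 33 per arm. Then 33 × 1.2 = 39.6, so 40 per arm. The stated figure reproduces. With 20% dropout, 40 × 0.8 = 32 completers per arm.

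**Step 2. Power of the planned test at the planned rates.** With 32 per arm and no control responders, Fisher's test needs 6 treated responders (p = 0.024; with 5, p = 0.053). The chance of 6 or more out of 32 at a 28% rate is 0.919. The planned test therefore has about 92% power on the protocol's own inputs.

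**Step 3. Sensitivity to the zero control rate.** Treated rate held at 28%, 32 per arm, exact enumeration of Fisher's test:

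| Control response | Fisher power |
|---|---|
| 0% | 92% |
| 1% | 85% |
| 5% | 61% |
| 10% | 34% |

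Section 9 gives neither the size of the previous study nor any uncertainty around its 0%.

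**Step 4. Efficiency of the category against the mean.** The protocol gives no SD, so this is a model: normal DBP change, equal SD, one responder cut-off. The standardised difference is d = z(1 − control rate) − z(1 − 0.28). At a 5% control rate, d = 1.645 − 0.583 = 1.06. The number per arm for 90% power is then 53 for the category and 19 for the mean, and 19/53 = 36%. At 1% it is 34 against 7 (21%); at 10%, 98 against 44 (45%); at 15%, 208 against 103 (50%). The category keeps roughly 20–50% of the efficiency. The real definition has two routes to response, so a single cut-off is an approximation.

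**Step 5. Illustration with baseline adjustment.** Assumptions, none from the protocol: 32 per arm, DBP SD 9, baseline-to-week-8 correlation r of 0.6 or 0.7, mean baseline 88 or 92, true difference 5 mmHg, normal taken as below 90, response as a fall of at least 10 or a fall from at least 90 to below 90.

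Closed form for the mean comparisons, where the SE is SD × √(2/32) = SD × 0.25:
- Week-8 t test: SE = 2.25; 5/2.25 = 2.22; power ≈ Φ(2.22 − 1.96) = 60%.
- ANCOVA, r = 0.6: residual SD = 9 × √(1 − 0.36) = 7.2; SE = 1.80; 5/1.80 = 2.78; power ≈ Φ(0.82) = 79%.
- ANCOVA, r = 0.7: residual SD = 9 × √(1 − 0.49) = 6.43; SE = 1.61; 5/1.61 = 3.11; power ≈ Φ(1.15) = 88%.

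Simulation agrees. Ranges cover the two baseline means, repeated runs and the approximations above:

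| | r = 0.6 | r = 0.7 |
|---|---|---|
| Control response | about 19% | about 16% |
| Treated response | 36–38% | 34–36% |
| Fisher on the category | 26–31% | 32–37% |
| t test on week-8 DBP | 57–61% | 57–61% |
| ANCOVA on week-8 DBP | 77–79% | 86–88% |

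**The case against.** The strongest case against is that the protocol allows more than section 12 spells out. Blood pressure sits under Outcomes in the process chart, and the t/Wilcoxon sentence in section 18 reads naturally as a between-group test for continuous measures. A reader might infer that mean pressures are not outcomes at all, or that the systolic effect cannot be tested. The documents do not support either inference: an unadjusted comparison of mean DBP and SBP is open, but it is not named or fixed.

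A reader might also infer that the category wastes most of the trial's power. On the protocol's own 28% against 0% it does not (step 2). The low Fisher figures in step 5 rest on inputs that imply a 16–19% control response, a different scenario from the planned one, so the size of the loss in this trial cannot be established from the document.

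The main outcome is also a reasoned choice. It comes from a named guideline and the trial is sized on it. An unadjusted test in a randomised trial is valid; adjustment adds precision and does not correct an error. All of this stands.

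The last argument is that covariate adjustment can be left to a statistical analysis plan, which is not shown. That is partly right, since such a plan may name these analyses. But the protocol itself sets the list of outcomes in section 12 and the tests in section 18, and those sections are where the pressures should be named.

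**Conclusion.** The point holds as one of outcome definition and efficiency. Section 12 names no between-arm outcome on mean DBP or SBP, SBP is outside the efficacy definition, and section 18 states only unadjusted tests although baseline values are collected. Firm figures, from the protocol's inputs with 32 completers per arm: about 92% Fisher power at a zero control rate. If the treated rate stays at 28%, this falls to 85%, 61% and 34% at control rates of 1%, 5% and 10%. The ANCOVA gain (about 77–88% against 26–37% for Fisher) is illustrative and depends on the assumed SD, correlation, baseline mean and effect.

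The documents do not show that the trial is underpowered as planned. They also give no ground for replacing the main outcome, which would need a new sample-size basis. The change is worth making because it costs almost nothing and guards against a control response above zero.

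**What to change.** Keep the responder rate as the main outcome, with its current test and sample size.

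1. **Section 12, secondary outcomes:** add the between-arm difference in office DBP at week 8 and the between-arm difference in office SBP at week 8.
2. **Section 18:** analyse each by ANCOVA, with treatment arm as factor and the participant's own baseline value of that pressure as covariate. Report the adjusted difference with a 95% CI. Give the same analysis at week 4 as supportive.

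The cost is a change of wording in two sections and two extra secondary models, repeated at week 4. There are no new visits, measurements or participants. The downside is two more secondary results to report, which should be labelled as secondary to the responder rate.
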